### Statistical methods

#### Primary efficacy endpoint analysis for the main part of the trial

The primary efficacy endpoint of the trial, LRC-survival over two years, will be tested for superiority of the experimental arm over the comparator arm using the one-sided Log-rank test at the 0.05 significance level on the ITT set. LRC-survival is defined as time to local relapse or death calculated from start of radiotherapy.

The corresponding hypotheses are:

H0: Se(t) ≤ Sc(t) vs. Ha: Se(t) > Sc(t),

Se and Sc denote the two-year LRC-survival in the experimental arm and in the control arm respectively.

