## Background

Head and neck cancers are the seventh most frequent cancer in Germany (estimated incidence of 50/100.000 per year, Deutsche Krebsgesellschaft). The German Robert-Koch-Institut presented recently data on absolute disease numbers of all tumor entities. In 2013 for head and neck cancer there were 4.500 women and 13.000 men newly diagnosed in Germany [1]. For 2020 the new diagnosis expectations are higher: women 5.500 and men 14.300. Worldwide there are more than 550.000 new cases every year [2].

Head and neck cancers are representative for solid tumours in which new biological-imaging-based treatment strategies can be tested comparatively easily. This is true especially with regard to the impact of tumour volume, which correlates with cell number per tumour and tumor hypoxia, on response after non-surgical treatment.

Concomitant chemo-irradiation is superior to radiation alone in inoperable LAHNSCC. An absolute survival benefit of 8% at 5 years favouring chemo-irradiation was shown in the meta-analysis of the MACH-NC-group (2000) [3]. The up-date of the MACH- NC-group in 2009 included studies between 1994 and 2000. Again there was an absolute benefit of 6.5% for chemo-irradiation (independent of the setting – postoperative or primary chemo-irradiation) concerning the HR of death in comparison to local treatment alone [4]. In 2011 the MACH-NC group investigated the effect of chemo-irradiation in comparison to radiotherapy and revealed a 5-year absolute benefit (OS) due to concomitant chemotherapy for oral cavity: 8.9%, oropharynx: 8.1% and 4% for hypopharynx [5].

Besides tumor volume correlating with cell number per tumor, hypoxia is a further important biological parameter for tumor progression. Hypoxia increases radio-resistance and is a predictive factor for local failure. Hypoxia occurs in about 80% of head and neck tumors (primaries and/or lymph nodes). Based on experimental and clinical data, hypoxia is considered as a useful parameter for pre-therapeutic stratification in future randomized chemo-irradiation trials. More importantly, hypoxic sub-volumes of tumors are also evolving as target volumes for radiotherapy (“dose painting”) in some studies examining the significance of selective irradiation dose escalation. To investigate the shift of the hypoxic sub-volumes [18 F]-FMISO PET will be performed twice within 1 week before start of radiation treatment.

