### Imaging

During screening the standard staging program to exclude lung and liver metastasis or secondary cancer is performed by CT Thorax and ultrasound of the liver.

CT or MRI of the head and neck is performed at the time of screening and then at every follow-up visit using the RECIST-criteria version 1.1.

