***GTV)***
**:** The description of the gross tumor volume is based on CT and optionally MRI scan, endoscopic and clinical examinations as well as additional imaging.

A lymph node should be classified as involved, if it has/there arediameter ≥ 1 cm (jugulo-digastric lymph nodes >1.1–1.5 cm) in the first echelon of the tumordiameter ≤ 1 cm with spherical shape in the first echelon of the tumorlymph nodes containing necrotic areasmultiple (minimal 3) lymph nodes of the ipsilateral neck of the primary tumor.

All these lymph nodes should be delineated for GTV.

***Clinical target volume (CTV)*** is defined as the GTV plus regions classified to be at risk for microscopic spread. The extension of this volume is determined by the radio-oncologist.

**CTV 70** is defined as GTV of the primary tumor plus 1 cm and GTV of the involved lymph nodes plus 0.5 cm but for cranio-caudal direction also 1 cm (for control group and for experimental group).

**CTV 56** is defined as elective lymph node levels (for control group and for experimental group).

***Planning target volume (PTV)*** here deemed as SIB 56 and SIB 70 for experimental and control group.

**SIB 56** is defined as an additional set-up margin around CTV 56 in all directions to compensate for morphological changes (i.e. weight loss), set-up deviation and internal organ motion.

0.5 cm as safety margin is recommended for the upper cervical structures and 0.7 cm for the lower cervical structures. Exceptions are the direct neighborhood of critical organs as the spinal cord or other organs at risk.

A skin sparing of 0.3 cm is recommended unless the tumor invades near the skin or e.g. into the sternocleidomastoid muscle.

In addition, the set-up margin should be defined according to the results on set-up error for IMRT at each participating center.

The **SIB 70** will be derived from the CTV 70 (automatically contoured margins by the planning system) as described above. The SIB 70 has to be adapted by hand at each planning CT slice to organs at risk and anatomical boundaries.

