## Statistics

### Sample size calculation

Sample size calculations are based on the Log-rank test for superiority of the experimental arm over the comparator arm in LRC-survival over two years. The two-year LRC-survival is expected to be about 60% in the comparator group and about 75% in the experimental group. When the sample size in each group is 125, the one sided Log-rank test will have power of about 80% to detect the assumed difference at the 0.05 level. Therefore, 250 patients need to be recruited in the trial, 125 in each arm.

Due to missing alternative therapy concepts in non-resectable LAHNSCC, the expected compliance rate will be over 95%. Missing values will be conservatively treated: In the control arm, missing values will be imputed by the longest observed loco-regional survival time. In the experimental arm, missing values will be set to the time of censoring.

Because of the pre-study requirements of the BfS the pre-study will include 20 patients. These 20 patients are on top of the calculated 250 patients for the whole trial.

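### The primary log-rank test leaves baseline tumour size unused; a pre-specified stratified or adjusted test could add about 0 to 5 power points at low cost

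*Protocol article*

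**What the plan says.** The section on the primary efficacy endpoint analysis fixes the comparison "using the one-sided Log-rank test at the 0.05 significance level on the ITT set". The endpoint is time to local relapse or death. No stratification factor or covariate is named there.

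The sample size section powers the same plain test: "The two-year LRC-survival is expected to be about 60% in the comparator group and about 75% in the experimental group", and "When the sample size in each group is 125, the one sided Log-rank test will have power of about 80" per cent. It concludes that "250 patients need to be recruited in the trial, 125 in each arm".

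On tumour size, three places matter:

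- The Background singles out "the impact of tumour volume, which correlates with cell number per tumour and tumor hypoxia, on response after non-surgical treatment".
- The Imaging section states that "CT or MRI of the head and neck is performed at the time of screening"; the section on evaluation of therapy outcome repeats this.
- Under target volumes, "The description of the gross tumor volume is based on CT and optionally MRI scan". The 70 Gy clinical target volume is built from the GTV in both the control and the experimental group, so a contour is needed in each arm.

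**The concern.** When a baseline variable predicts the outcome and can be obtained in both arms, using it in the primary test normally raises power without affecting type I error. Here the protocol itself gives a reason to expect tumour volume to be prognostic, and the images and contours exist for treatment purposes. Yet the named test does not use them.

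This is a stated choice rather than an open detail: an analysis plan that added a covariate would change the primary test as written. What is at stake is efficiency in a 250-patient trial that was planned with only a small margin above its power target.

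**Working it through.** **Inputs from the protocol article.** 125 patients per arm; two-year LRC-survival of 60% and 75%; one-sided level 0.05; follow-up of at least two years.

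**Step 1: the stated power.** With proportional hazards, HR = ln(0.75)/ln(0.60) = 0.563. Expected events by two years = 125 × 0.40 + 125 × 0.25 = 81.25.

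- Freedman: z = √81.25 × (1 − 0.563)/(1 + 0.563) − 1.645 ≈ 0.87, so power is 80.9%. This needs 80 events, about 123 per arm.
- Schoenfeld: z = √(81.25/4) × |ln 0.563| − 1.645 ≈ 0.94, so power is 82.7%.

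The stated figure of about 80% is reproduced.

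**Step 2: what adjustment would add.** The document gives no hazard ratio for tumour volume, so a range is assumed. The simulation used 6,000 trials per setting, exponential times, censoring at two years and a standard normal log volume. The marginal rates were held at 60% and 75%. Power in per cent:

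| Assumed HR per SD of log volume | Log-rank | Log-rank, 3 volume strata | Cox with log volume | Cox gain (points) |
|---|---|---|---|---|
| 1.25 | 82.3 | 82.1 | 82.4 | 0.1 |
| 1.5 | 82.1 | 83.2 | 83.9 | 1.8 |
| 1.75 | 83.0 | 85.4 | 86.3 | 3.3 |
| 2.0 | 82.3 | 86.2 | 87.6 | 5.3 |
| 2.5 | 83.3 | 88.9 | 91.4 | 8.1 |

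The Monte Carlo standard error of one entry is √(0.82 × 0.18/6000) ≈ 0.5 points. A second simulation of 4,000 trials per setting agreed: 82.3 to 83.6 at HR 1.5, 82.1 to 86.2 at 1.8, 81.7 to 87.2 at 2.0, and under 1 point at 1.3. With no treatment effect, the one-sided rejection rate lay between 4.3% and 5.4% for all tests. The last row is shown for completeness; the conclusion uses 1.3 to 2.0.

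**Step 3: two features of this trial that shrink the gain.** Deaths from any cause are events, and the Discussion notes that non-cancer deaths are common in these patients. The Discussion also suggests a flatter dose response in large tumours, so the treatment effect may vary with volume. Power was recomputed with 4,000 trials per setting under assumed sizes for each feature:

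| Setting (assumed) | HR 1.3 | HR 1.5 | HR 1.8 |
|---|---|---|---|
| 30% of mean control hazard unrelated to volume: unadjusted → Cox | 82.5 → 82.4 | 82.2 → 82.6 | 81.9 → 83.4 |
| Volume-by-arm interaction, log-HR 0.2 per SD: Cox gain | 0.1 | 0.1 | 2.0 |

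Over the range 1.3 to 2.0, the gain in these two settings is about 0 to 3 points. No setting showed a material loss of power.

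**The case against.** The strongest reply is that nothing here is wrong. The unadjusted log-rank is valid, matches the test used for the sample size and meets its power target. That stands, and it limits the point to efficiency.

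A second objection concerns the covariate. The article does not say that a GTV volume is recorded as trial data, and the RECIST reading of the CT or MRI yields diameters. Nor does it say that contouring precedes randomisation. In the experimental arm the GTV also defines the escalated volume, so a contour drawn by someone who knows the arm is not a clean baseline value. Patients in the ITT set who never reach planning would have no contour. These points stand and shape the fix.

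A third is that covariates are often left to an analysis plan. This carries less weight, because the primary test is named here without any.

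Three stronger readings are tempting but not supported:

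- *That volume is the main driver of response and is measured in every patient.* The Background speaks of its impact and calls hypoxia a further important parameter; it does not rank volume first. Measurement is inferred from imaging and contouring.
- *That adjustment is needed to keep 80% power.* With an assumed 5% loss, uniform over two years, and the protocol's imputation rule, simulated unadjusted power was about 77 to 79%. Cox-adjusted power was 80%, 82% and 85% at HR 1.5, 1.8 and 2.0. But the document states only that "the expected compliance rate will be over 95" per cent, which is not a loss rate. The shortfall also comes from the imputation rule, a separate matter.
- *That chance imbalance in volume would invalidate the comparison.* In the roughly 16% of simulated trials with an imbalance of more than one standard error against the experimental arm, unadjusted power fell to 74% at HR 1.5 and 66% at 2.0. Those draws are already counted in the overall power, and the type I error covers chance imbalance.

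**Conclusion.** The point holds as a missed efficiency gain. The primary test uses no baseline covariate although the protocol names one that it believes matters and that can be obtained in both arms. The size is uncertain: about 0 to 5 power points for assumed hazard ratios of 1.3 to 2.0 per SD of log volume, and about 0 to 3 under the two less favourable settings. These figures rest on assumed prognostic strength, exponential times and a log-linear volume effect. If volume is only weakly prognostic, adjustment gains almost nothing and loses almost nothing. The trial is neither invalid nor short of its stated power on this account.

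**What to change.** Before outcome data are seen, state that the primary test is a one-sided log-rank stratified by pre-specified classes of baseline tumour size, or a one-sided test of treatment in a Cox model with log baseline tumour size. Keep the unadjusted log-rank as a sensitivity analysis. The stratified log-rank stays closest to the current test and keeps most of the gain (86.2% against 87.6% for Cox at HR 2.0).

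State the source of the value: the screening CT or MRI obtained before randomisation, or a GTV contoured without knowledge of the arm. State also the category for ITT patients who lack it. Because of the Discussion's remark on large tumours, explore a volume-by-arm interaction as a secondary analysis.

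The cost is a few sentences and no new patient procedure, but the change is not free. The size must be extracted from existing images or contours, and the classes or functional form must be fixed in advance. A Cox model also reports a conditional hazard ratio: in the simulation 0.552 at HR 1.5 and 0.531 at 2.0, against 0.563 with no volume effect.

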### Hypothesis of the trial

Over the last decade IMRT became a new standard in radiotherapy. Different trials used the advantage of IMRT concerning target volume coverage and protection of organs at risk. Analyses of acute toxicity of IMRT revealed advantage for lower toxicity compared to 3D-conformal radiotherapy with comparable treatment results.

The 2-year local control rate varies between 77–98% and the loco-regional control at 2 years between 86%–100% for non-selected tumor stages [6–8]. Two studies reported 2-year overall survival between 90–94% [9, 10] for patients with locally advanced disease.

The ESCALOX trial investigates whether dose-escalated SIB-IMRT to the primary tumor and involved cervical lymph nodes (≥2 cm) with concurrent cisplatin chemotherapy improves loco-regional control within 2 years by 15% in comparison to conventional SIB-IMRT with concurrent cisplatin.

The experimental arm of the ESCALOX-trial has not yet been tested in a multi-institutional setting. Taking into account all the mentioned results on acute and late toxicity it seems possible to apply dose escalated radiotherapy with optimization of the IMRT-plan concerning the organs at risk.

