**Fig. 1 Fig1:**
[figure not shown]
ESCALOX - Trial scheme

IMRT or VMAT will be performed to apply the RT as simultaneous integrated boost. The ESCALOX trial enrols patients with LAHNSCC of the oral cavity, oropharynx or hypopharynx. Patients will be treated by the University Departments of Radiation Oncology and Radiation Therapy in Germany.

The primary endpoint of the pre-study as recommended by the German Federal Office of Radiation Protection (BfS) will be the assessment of acute toxicity. The primary endpoint of the main study is the local-regional control (LRC) at 2 years.

The secondary endpoints are disease-free survival (DFS), progression-free survival (PFS), overall survival (OS), acute and late radiation effects, adverse events, tumor hypoxia status investigated by 18-F-FMiso-PET.

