## Safety

### Safety pre-study

The federal office of radiation protection (BfS) requires the successful completion of a pre-study before the main study is allowed to recruit patients.

The pre-study is planned to be carried out as follows:

A pre-study was initiated before starting treatment according to ESCALOX’s planned study arms (arm A: the experimental group receiving a dose escalation up to 80.5 Gy and arm B: the control group receiving a standard dose up to 70.0 Gy).

The pre-study is analogue to the experimental group A but the dose-escalation to the macroscopic tumor and involved lymph nodes ≥ 2 cm is restricted to 2.2 Gy up to a total dose of 77.0 Gy in this SIB-volume.

In the first step 6 patients will be treated up to 77.0 Gy. After the last patient finished the RT-course there was an interval of 6 weeks defined to assess acute toxicity. When the last patient has finished the 6 weeks of follow-up and no more than 1 of the 6 patients reached grade 4 radiation induced toxicity (CTCAE v. 4.0), further 14 patients will be allowed to enter the pre-study. For all of these 20 patients the 6 weeks follow-up is fixed to assess acute toxicity as mentioned above. If no more than 2 out of all 20 patients reached grade 4 toxicity (CTCAE v. 4.0) at this time (6 weeks after end of treatment) recruitment for the main part of the ESCALOX trial with randomization into arms A and B is allowed to begin.

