#### Pre-Study: Special Definition of dose escalated planning target volume (SIB 77.0) for the pre-study group in step-wise recruitment

**Dose escalated volume (deemed as SIB 77.0):** The dose escalated volume is defined as the gross tumor volume (GTV) of the primary tumor (PT) and all involved lymph nodes (LN) with a minimal axial diameter > 2 cm. At critical structures (e.g. mucosal sites, vessels, skin) the GTV is reduced by 0.3 cm (inner margin). Treatment planning will be performed without set-up error for the SIB 77.0.

All lymph nodes detected as involved with a minimal axial diameter of 2 cm will be also included as SIB 77.0.

For definition of SIB 70 and SIB 56 see above (Planning target volume (PTV) here deemed as SIB 56 and SIB 70).

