#### Missing data

Missing values will be conservatively imputed for the assessment of the primary endpoint: In the control arm, missing values will be imputed by the longest observed loco-regional survival time. In the experimental arm, missing values will be set to the time of censoring. The primary endpoint will also be analyzed as a secondary endpoint without imputation. Imputation is not performed for the secondary endpoints.

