## Abbreviations

AF: Accelerated Fractionation
AF + ccb: Accelerated Fractionation with Concomitant Boost
ARO: Arbeitsgemeinschaft Radioonkolgie
AUC: Area under the curve
BfArM: Bundesinstitut für Arzneimittel und Medizinprodukte (German Federal Institute for Drugs and Medical Devices)
BfS: Bundesamt für Strahlenschutz (German Federal Office of Radiation Protection)
CT: Computertomography
CTCAE: Common Toxicity Criteria Adverse Events
CTV: Clinical Target Volume
DFS: Disease Free Survival
DVH: Dose Volume Histogram
FDG: Fluorodesoxyglucose
FMISO: Fluoromisonidazol
GTV: Gross Target Volume
Gy: Gray
HF: Hyper-fractionation
IIT: Investigator initiated trial
IMRT: Intensity Modulated Radiotherapy
IMSE: Institut für Medizinische Statistik und Epidemiologie
*i*RT: Institut für Innovative Radiotherapie
LAHNSCC: Locally Advanced Head and Neck Squamous Cell Cancer
LRC: Loco-regional Control
MRI: Magnetic Resonance Imaging
MSZ: Münchner Studienzentrum
NF: Normo-fractionation
OAR: Organs at Risk
OS: Overall Survival
PET: Positron Emission Tomography
PFS: Progression Free Survival
PTV: Planning Target Volume
RT: Radiotherapy
RTOG: Radiation Therapy Oncology Group
SIB: Simultaneous Integrated Boost
VMAT: Volumetric Arc Therapy

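### The only definition of the primary event says local relapse or death, while the endpoint is named loco-regional control; the two must be reconciled

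*Protocol article*

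**What the plan says.** The definition is in Statistical methods, under the primary efficacy endpoint analysis: "LRC-survival is defined as time to local relapse or death calculated from start of radiotherapy". It is the only place where the article says what counts as a primary event.

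The endpoint is named differently elsewhere:

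- Study design: "The primary endpoint of the main study is the local-regional control (LRC) at 2 years".
- Hypothesis of the trial: the question is whether "dose-escalated SIB-IMRT to the primary tumor and involved cervical lymph nodes (≥2 cm) with concurrent cisplatin chemotherapy improves loco-regional control within 2 years".
- Missing data: "In the control arm, missing values will be imputed by the longest observed loco-regional survival time". The sample size section carries the same rule.
- Abbreviations: "LRC: Loco-regional Control".

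On what is escalated, the pre-study safety section refers to "the dose-escalation to the macroscopic tumor and involved lymph nodes ≥ 2 cm". The definition of the escalated volume, which the experimental arm of the main study takes over, includes "all involved lymph nodes (LN) with a minimal axial diameter > 2 cm".

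The sample size section assumes two-year LRC-survival of 60% (control) and 75% (experimental), with 125 patients per arm, a one-sided log-rank test at 0.05 and power of about 80%. The head and neck is imaged by CT or MRI at every follow-up visit, read by RECIST 1.1.

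**The concern.** In head and neck oncology, local refers to the primary site and regional to the neck nodes. The article keeps the two apart itself: Hypothesis of the trial quotes one published range for local control (77–98%) and a separate one for loco-regional control (86–100%). The word local in the event definition therefore cannot simply be assumed to include the neck.

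If the definition is applied as printed, an isolated nodal failure is not an event on the day it is found. It enters the analysis only through a later local relapse or death. The treatment under test raises the dose to larger involved nodes as well as to the primary, so the test would leave out one kind of failure that the treatment is meant to prevent and that the hypothesis names. If the wording stays open, whether nodal failures count could also be settled after data have been seen.

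**Working it through.** **1. The texts side by side.** The endpoint name, the hypothesis, the imputation rule and the abbreviation list all say loco-regional. The event definition alone says local. No sentence states that regional or nodal relapse counts. The conflict is therefore in the text itself and is not a detail left to a fuller document.

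**2. The plan's own sample size.** Inputs from the sample size section: 60% and 75% at two years, 125 per arm, one-sided 0.05.

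- HR = ln(0.75)/ln(0.60) = 0.563.
- Expected events by two years = 125 × 0.40 + 125 × 0.25 = 81.25.
- Power by Freedman = Φ(√81.25 × (1 − 0.563)/(1 + 0.563) − 1.645) = 80.9%.
- Power by Schoenfeld = Φ(√81.25 × |ln 0.563|/2 − 1.645) = 82.7%.
- Freedman needs 80 events for 80% power. The average two-year event risk is (0.40 + 0.25)/2 = 0.325, and 80/0.325 = 246.2, so 247 patients against 250 stated.

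The stated size reproduces, with little to spare.

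**3. Illustration of the literal definition.** The article gives no share of regional-only failures, so the share f is assumed. Let f be the fraction of two-year events, equal in both arms, that are regional-only and are not followed by local relapse or death within two years. The two-year rates become 1 − 0.40(1 − f) and 1 − 0.25(1 − f). HR is the ratio of their logarithms, and events are 81.25(1 − f).

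| f | Two-year rates | HR | Events | Power, Freedman | Power, Schoenfeld |
|---|---|---|---|---|---|
| 0 | 60% / 75% | 0.563 | 81.25 | 80.9% | 82.7% |
| 5% | 62% / 76.2% | 0.567 | 77.2 | 78.3% | 80.1% |
| 10% | 64% / 77.5% | 0.571 | 73.1 | 75.5% | 77.3% |
| 20% | 68% / 80% | 0.579 | 65.0 | 69.4% | 71.3% |
| 30% | 72% / 82.5% | 0.586 | 56.9 | 62.8% | 64.5% |

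**4. Milder variant.** Patients with nodal failure stay at risk of local relapse and death. If the same share is taken off the hazard instead, the rates become 0.60^(1 − f) and 0.75^(1 − f), with HR still 0.563.

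- f = 10%: 125 × (2 − 0.60^0.9 − 0.75^0.9) = 74.6 events, Schoenfeld power 79.8%.
- f = 30%: 125 × (2 − 0.60^0.7 − 0.75^0.7) = 60.4 events, Schoenfeld power 72.1%.

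This lets some patients with nodal failure return as later events, so the loss is smaller than in step 3.

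**The case against.** The best defence is that local relapse is loose shorthand in a condensed article. The quantity being defined is called LRC-survival, LRC is expanded as loco-regional control, and the imputation rule for the same endpoint speaks of loco-regional survival time. This is plausible and may well be what was meant. It makes the point easier to correct but does not remove it, because the sentence is the only definition and the article elsewhere separates local from loco-regional control.

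Several stronger readings are tempting, and the document does not support them:

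- *The trial deliberately excludes the neck.* Nothing says so, and the endpoint's name points the other way.
- *The test ignores half of the treatment effect.* No split between primary and nodal benefit is given. Only involved nodes of about 2 cm or more are escalated (the article writes both ≥ 2 cm and > 2 cm, which does not affect this point).
- *The trial is underpowered.* The 60% and 75% carry the label LRC-survival and may already mean loco-regional failure or death. The power losses above depend on an assumed share.
- *Loco-regional control will be overstated in both arms.* The literal definition misses or delays nodal failures but also counts every death, which lowers the figure relative to pure loco-regional control. The net direction is not established.
- *Tumour that never clears is wrongly left out.* How persistent disease is classified and dated can properly sit in the full protocol or analysis plan, which are not shown.

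**Conclusion.** The point holds as an internal contradiction in the definition of the primary event. As printed, isolated nodal failure does not count until local relapse or death, while the hypothesis and the endpoint's name include it. It should be corrected because the confirmatory test depends on this sentence, even if the cause is only a slip of wording.

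Its numerical effect cannot be fixed from the document. Under the assumed 10% to 30% share of regional-only events never followed by local relapse or death within two years, power would fall by about 5 to 18 percentage points (80.9% to 75.5% and to 62.8% by Freedman; 82.7% to 77.3% and to 64.5% by Schoenfeld). Where such patients later relapse locally or die within two years, the loss is smaller. If the shorthand reading is right and is followed in practice, there is no loss and only the sentence is wrong.

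**What to change.** In the primary efficacy endpoint section, define the event as the first of local failure, regional (nodal) failure, or death as now stated, with failure read by RECIST 1.1 on the head and neck imaging already scheduled. Use that one definition in the design, sample size, analysis and missing-data sections.

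Also state that the 60% and 75% two-year figures refer to this event. If they do, 250 patients is unchanged. If they were derived for local relapse or death only, the assumption has to be restated and the size recalculated.

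The cost is one sentence plus that confirmation. No additional visit or scan is needed.

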**Discussion:**

The primary endpoint of the pre-study is acute radiation induced toxicity. Primary endpoint of the main trial is 2-year-LRC. By using the dose escalation up to 80.5 Gy to the GTV of the primary tumor and lymph nodes > 2 cm a LRC benefit of 15% at 2 years should be expected. The ESCALOX trial is supported by Deutsche Forschungsgemeinschaft (DFG); Grant No.: MO-363/4-1.

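### The primary event is written as local relapse or death, while the endpoint is named loco-regional control; read literally, a neck-only relapse is not counted

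*Protocol article*

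**What the plan says.** The only operational definition of the primary variable is in the protocol article, under Primary efficacy endpoint analysis for the main part of the trial: "LRC-survival is defined as time to local relapse or death calculated from start of radiotherapy".

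Elsewhere the same endpoint is loco-regional:

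- Study design (text below Fig. 1): "The primary endpoint of the main study is the local-regional control (LRC) at 2 years".
- Hypothesis of the trial: the question is whether the experimental treatment "improves loco-regional control within 2 years by 15" per cent.
- Abbreviations: "LRC: Loco-regional Control".
- Sample size calculation, repeated under Missing data: in the control arm, "missing values will be imputed by the longest observed loco-regional survival time".

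The boost is not confined to the primary site. The Discussion paragraph of the Abstract describes the expected benefit as follows: "By using the dose escalation up to 80.5 Gy to the GTV of the primary tumor and lymph nodes > 2 cm". The special definitions of the SIB 77.0 and SIB 80.5 volumes likewise include involved nodes.

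**The concern.** In head and neck radiotherapy, local relapse usually means relapse at the primary site and regional relapse means relapse in the neck nodes. The endpoint's name covers both. Its definition covers the first, plus death.

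A blinded rater who applies the definition as written would leave a neck-only relapse uncounted and keep the patient at risk. A rater who follows the endpoint's name would count it. These two readings give different event times for the same patient, and the choice should not still be open when results exist.

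The omitted site is also one that the experimental arm treats. A failure inside a boosted node would reach the primary analysis only through a later local relapse or a death. Any gain or loss from nodal escalation would therefore be only partly reflected in the test on which the trial is judged.

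**Working it through.** **1. Are the two terms used as synonyms?** Under Hypothesis of the trial, the article gives a two-year local control range of 77–98% and then adds a second range, introduced by "and the loco-regional control at 2 years between", of 86–100%. The two are reported side by side as separate quantities. Nothing in the article says that local relapse is meant to include nodal relapse.

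**2. Does the planned power reproduce?** Inputs from Sample size calculation: two-year LRC-survival 60% (control) and 75% (experimental), 125 patients per arm, one-sided log-rank test at 0.05, power about 80%.

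- Hazard ratio under proportional hazards: ln(0.75)/ln(0.60) = 0.2877/0.5108 = 0.563.
- Expected two-year events: 125 × (0.40 + 0.25) = 81.25.
- Freedman: √81.25 × (1 − 0.563)/(1 + 0.563) = 2.519; 2.519 − 1.645 = 0.874; power = Φ(0.874) = 80.9%.

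The stated figure is reproduced. Freedman's formula requires 80 events, or about 246 patients, against the 250 planned.

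**3. What could the literal definition cost?** This step is illustrative. It assumes that 60%/75% are rates for loco-regional relapse or death, and that a share q of those events is node-only and not followed by local relapse or death in the window. The documents give no value for q, so 10%, 20% and 30% are assumptions.

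- Model A removes a share q of cumulative events in each arm. Two-year rates become 1 − 0.40(1 − q) and 1 − 0.25(1 − q), events become 81.25(1 − q), and the HR is recomputed from the new rates.
- Model B removes a share q of the hazard in each arm. Two-year rates become 0.60^(1 − q) and 0.75^(1 − q), and the HR stays at 0.563.

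| q (assumed) | A: control / experimental rate | A: HR | A: events | A: power | B: control / experimental rate | B: events | B: power |
|---|---|---|---|---|---|---|---|
| 0 | 60% / 75% | 0.563 | 81.25 | 80.9% | 60% / 75% | 81.25 | 80.9% |
| 10% | 64% / 77.5% | 0.571 | 73.1 | 75.5% | 63.1% / 77.2% | 74.6 | 77.9% |
| 20% | 68% / 80% | 0.579 | 65.0 | 69.4% | 66.5% / 79.4% | 67.6 | 74.3% |
| 30% | 72% / 82.5% | 0.586 | 56.9 | 62.8% | 69.9% / 81.8% | 60.4 | 70.1% |

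The models agree in direction and differ by 2.4 to 7.3 percentage points (77.9 − 75.5; 70.1 − 62.8). Deaths within the window reduce the loss. If half of the node-only patients die in that time, the effective share is halved, so the 20% row becomes roughly the 10% row.

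**The case against.** The strongest reply is that this is a slip of wording. The variable being defined is called LRC-survival, the abbreviation list expands LRC as loco-regional, and the hypothesis and the imputation rule say the same. One word in a condensed article stands against all of that, and nothing shows that the sponsor chose to exclude nodal relapse. This is probably right as to intent, and the point should be read as a contradiction to reconcile, not as a criticised design decision. It does not remove the point: the article states a rule, the rule is the only one given, and it differs from the name.

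A reader might infer that the 60%/75% rates do not match the event counted and that the trial therefore falls short of 80% power. The documents do not support that. The rates are given for LRC-survival, the very term that is later defined. If both places are read literally, or both as loco-regional, rate and event agree. A mismatch arises only if one is read each way. The article's own Discussion quotes loco-regional control of 40–65% after combined treatment, which makes a loco-regional source for the 60% plausible, but no source is stated.

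A reader might also infer that regional control drops out of the primary test altogether. That is too strong. Death is part of the composite, so fatal nodal failure still counts, and a nodal relapse followed by local relapse counts at the later date. DFS, PFS and OS are also listed as secondary endpoints, although these are analysed exploratively.

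**Conclusion.** The contradiction is established from the text alone. The definition under Primary efficacy endpoint analysis names local relapse and death. The hypothesis, the study design, the abbreviation list and the imputation rule all name a loco-regional quantity, and the article treats local and loco-regional as distinct. Because this decides what counts as a primary event in a phase III trial, it should be corrected before the primary endpoint is analysed.

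The sample-size arithmetic is not at fault. A power loss is possible but not shown, because it depends on which event the planning rates describe and on a node-only share that the documents do not give. Over assumed shares of 10–30%, power would lie between 77.9% and 62.8% depending on share and model, and nearer 80% if some of these patients die within two years. The need for one definition does not depend on these figures.

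**What to change.** Under Primary efficacy endpoint analysis, define LRC-survival as time from start of radiotherapy to local relapse, regional (cervical nodal) relapse or death, whichever comes first. Use the same wording under Study design, Sample size calculation and Missing data.

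State which event the 60% and 75% rates describe. If they already describe loco-regional relapse or death, the sample size stands as calculated. If they were derived for relapse at the primary site or death, they need to be justified again for the wider event, which is more than a wording change.

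No scans, visits or patients are added by the redefinition itself: CT or MRI of the head and neck is already planned at every follow-up visit (Imaging; Evaluation of therapy outcome). Reporting primary-site and nodal failures as separate components would be useful but is optional.
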